## GLOSSARY OF ABBREVIATIONS

|               |                                                                                                               |
|---------------|---------------------------------------------------------------------------------------------------------------|
| AE     | Adverse Event                                                                                          |
| ASR    | Annual Safety Report                                                                                   |
| BASEC  | Business Administration System for Ethical Committees                                                  |
| CGM    | Continuous Glucose Monitor                                                                             |
| CHO    | Carbohydrates                                                                                          |
| ClinoO | Ordinance on Clinical Trials in Human Research (in German: KlinV, in French: OClin, in Italian: OSRUm) |
| CRF    | Case Report Form                                                                                       |
| CTCAE  | Common Terminology Criteria for Adverse Events                                                         |
| CV     | Coefficients of Variation                                                                              |
| DD     | Device Deficiency                                                                                      |
| EC     | Ethics Committee                                                                                       |
| eCRF   | electronic Case Report Form                                                                            |
| EFSD   | European Foundation for the Study of Diabetes                                                          |
| FADP   | Federal Act on Data Protection (in German: DSG, in French: LPD, in Italian: LPD)                       |
| FOPH   | Federal Office of Public Health                                                                        |
| GCP    | Good Clinical Practice                                                                                 |
| GLM    | General Linear Models                                                                                  |
| HRA    | Human Research Act (in German: HFG, in French: LRH, in Italian: LRUm)                                  |
| ICH    | International Conference on Harmonisation                                                              |
| SAE    | Serious Adverse Event                                                                                  |
| SCTO   | the Swiss Clinical Trial organization                                                                  |
| SD     | Standard Deviation                                                                                     |
| SNCTP  | Swiss National Clinical Trial Portal                                                                   |
| SSL    | Secure Sockets Layer                                                                                   |
| WHO    | World Health Organization                                                                              |

# 1 BACKGROUND AND RATIONALE

Diet and physical activity are critically important in the lifestyle of people with type 1 diabetes. When diagnosed with the disease, people with type 1 diabetes are educated about nutritional goals and how to estimate nutritional content of food. Carbohydrates are the food component with the greatest impact on blood glucose levels and typical sources in the diet include starches, some vegetables, fruits, dairy products and sugars [1]. Thus, people with type 1 diabetes are primarily being trained to estimate the carbohydrate content of food, a task that is also referred to as carbohydrate counting. Different methods can be used to count carbohydrate in food and drink. These include reading the nutritional labels, consulting reference books or websites, carrying a database on a personal digital assistant or using exchange tables which provides the carbohydrate content for typical serving sizes (e.g. 1 slice of bread). While nutritional information can be accessed through the above mentioned methods, the quantification of the portion sizes (if not indicated on the food package) requires the additional use of scale or measuring vessel. Given the required effort and time investment related to these methods, the great majority of people with type 1 diabetes count carbohydrates by visual estimation and experience. As a consequence, people's estimate often deviate substantially from ground truth values and average carbohydrate estimation errors reported in the literature are 20% or higher [2].

Of note, more than 60% of individuals with diabetes report having trouble with carbohydrate counting, despite their awareness on its importance [3]. Even in patients who are confident in applying carbohydrate counting, the daily task is perceived as major burden of diabetes self-management [4].

Since carbohydrate counting is particularly demanding when eating fresh, non-packaged foods, a concerning trend towards unhealthy dietary choices with preference of prepackaged foods (with accessible nutrition facts) over whole foods is increasingly observed in people with type 1 diabetes [5, 6]. This is paralleled by an increasing prevalence of overweight and obesity in the type 1 diabetes population [7].

Thus, even with the latest hybrid closed-loop insulin delivery technologies, adequate nutrition knowledge remains a cornerstone for satisfactory glucose control, metabolic health, and prevention of diabetes-related complications and comorbidities [8].

With the development of new technologies embedded in modern smartphones (i.e. depth sensors), image-based methods to support food assessment have become widely available. Of particular use is the employment of well-established computer vision methodologies to estimate the quantity of food. When combined with food-recognition technologies and information from nutritional databases, a proposition of the nutritional content (e.g. carbohydrates, fat, proteins, fibres) can be made to the user on the basis of captured images and obviates the need for error prone visual estimations and mental calculations. Several such applications have become available and can support monitoring the diet as part of lifestyle management.

Insights from a recent online survey suggest that a high proportion of people with type 1 diabetes believe that such new technologies for meal management could facilitate their daily self-management and would be interested in using such technology. Moreover, according to a recent study, such digital tools may promote diabetes education and food literacy which may particularly benefit those with a lower education level and with a history of depression [4].

Amongst several options (e.g. Foodvisor, Calorie-Mamma, Lifesum) for image-based food tracking and analysis, SNAQ is one of the most commonly used app in people with type 1 diabetes. Up to date, more than 40000 users have downloaded the SNAQ app in their phones, of which 2,500 are living in Switzerland.

We have previously demonstrated that the system estimates the macronutrient content of real meals with satisfying accuracy [9].

However, evidence with regards to the effect of the food analysis on daily self-management of people with type 1 diabetes (e.g. glucose control, meal patterns, perceived benefits) is currently lacking. We therefore aim to address these aspects in a randomized-controlled study contrasting the use of the SNAQ app with people's traditional meal management techniques.

## 2 STUDY OBJECTIVES AND DESIGN

### 2.1 Hypothesis and primary objective

#### *Hypothesis*

The null hypothesis that there is no difference in the true mean time spent in the target glucose range (3.9 to 10.0mmol/L), will be tested against the alternative hypothesis that the use of the food analysis app, SNAQ, for meal management is superior to traditional meal management (two-sided alternative).

#### *Primary objective*

The primary objective is to assess the efficacy of the food analysis app, SNAQ, to improve glucose control in people with type 1 diabetes.

#### *Further objectives*

Further objectives are to assess the sustainability of potential improvements, the usability of the food analysis app, SNAQ, as well as its impact on nutrition literacy.

#### **Primary endpoint:**

*The primary objective will be addressed by evaluating the following endpoint:*

- 1) Percentage of time with sensor glucose in the target range (3.9 to 10.0mmol/L, %)

Note: Time in target range will be calculated over the complete 3-week intervention period (Day 1 to Day 21).

#### **Secondary endpoints:**

*The following endpoints will be assessed to evaluate the effect on glucose control:*

- 2) Percentage of time with sensor glucose in hyperglycaemia (>10.0mmol/L, %)

Note: Time in hyperglycaemia during the intervention period will be calculated over the 3-week intervention period (Day 1 to Day 21).

- 3) Percentage of time with sensor glucose in hypoglycaemia (<3.9mmol/L, %)

Note: Time in hyperglycaemia during the intervention period will be calculated over the 3-week intervention period (Day 1 to Day 21).

*The following endpoints will be assessed to evaluate the effect on postprandial glucose control:*

- 4) Percentage of postprandial time with sensor glucose in target range (3.9 to 10.0mmol/L, %).

Note: Time in target range during the intervention period will be calculated over the 3-week intervention period (Day 1 to Day 21). Postprandial periods are defined as the 180 min following main meal intake. Main meals are defined as CHO amounts above 25g entered by the participants in the hybrid closed-loop system.

- 5) Percentage of postprandial time with sensor glucose in hyperglycaemia ( $>10.0\text{mmol/L}$ , %).

Note: Time in hyperglycaemia during the intervention period will be calculated over the 3-week intervention period (Day 1 to Day 21). Postprandial periods are defined as the 180 min following main meal intake. Main meals are defined as CHO amounts above 25g entered by the participants in the closed-loop system.

- 6) Percentage of postprandial time with sensor glucose in hypoglycaemia ( $<3.9\text{mmol/L}$ , %).

Note: Time in hypoglycaemia during the intervention period will be calculated over the 3-week intervention period (Day 1 to Day 21). Postprandial periods are defined as the 180 min following main meal intake. Main meals are defined as CHO amounts above 25g entered by the participants in the hybrid closed-loop system.

*The following endpoints will be assessed to evaluate the sustainability of potential improvements:*

- 7) Change in the percentage of time with sensor glucose in target range ( $3.9$  to  $10.0\text{mmol/L}$ , %)
- 8) Change in the percentage of time with sensor glucose in hyperglycaemia ( $>10.0\text{mmol/L}$ , %)
- 9) Change in the percentage of time with sensor glucose in hypoglycaemia ( $<3.9\text{mmol/L}$ , %)
- 10) Change in the percentage of time with postprandial sensor glucose in target range ( $3.9$  to  $10.0\text{mmol/L}$ , %).
- 11) Change in the percentage of time with postprandial sensor glucose in hyperglycaemia ( $>10.0\text{mmol/L}$ , %).
- 12) Change in the percentage of postprandial time with sensor glucose in hypoglycaemia ( $<3.9\text{mmol/L}$ , %).

Note: For all outcomes evaluating sustainability of the improvements, glucose control endpoints calculated at baseline and in the 3 weeks period of SNAQ use will be compared with the variables calculated during the 3 weeks following discontinuation of the app. Baseline glucose control endpoints will be calculated over the 14 days prior to randomization (day -14 to day -1). Glucose control endpoints during the 3 weeks following discontinued use of the SNAQ app will be calculated as follow: Visit 2 + 1 Day to Visit 2 + 21 Days for the intervention group and Visit 3 + 1 Day to Visit 3 + 21 Days for the control group. Postprandial periods are defined as above.

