## **2.2 Study design**

### *Main study*

The study will follow a randomized two-arm parallel design. Study visits will be done remotely via video calls or in-clinic when coinciding with usual care appointments. Following a baseline visit and before randomization, baseline characteristics and medical history of the participants will be collected (as detailed in section 4.3). Following randomization, the intervention group will use SNAQ app for the first 3 weeks while the control group will proceed without any modification/intervention by the study team. After the first 3 weeks, the control group will undergo 3 weeks of SNAQ app use (weeks 4-6). At the end of their respective SNAQ app periods (weeks 4-6 for the intervention group and weeks 7-9 for the control group), both groups will discontinue the use of SNAQ app for 3 weeks to assess sustainability of potential effects. Finally, both groups will be offered to use SNAQ app for 3 additional weeks as per their preference (follow-up period). The study design is illustrated in **Figure 1**.

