### **Visit 1 (end of period 1)**

Visit 1 will entail the following procedures:

- Acquisition of the data download from the closed-loop system
- Acquisition of the data download from the SNAQ app (intervention group only)
- Feedback questionnaire on the SNAQ app (intervention group only)
- Nutrition literacy questionnaire (intervention and control group)

At the end of the visit and throughout Period 2, participants in the intervention group will stop using SNAQ app. To ensure that participants of the intervention group will stop using the SNAQ app, the license of the app will be temporarily de-activated remotely. Before the use of the SNAQ app, participants of the control group will receive premium version of the app for 12 months (including 6 weeks of the study and excluding the period when the usage of the app is not intended regarding the participation group) assistance with the download of the app, registration with the assigned study ID and a short guidance through the app given by the team, using the informational material provided by SNAQ app.

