### **Visit 2 (end of period 2)**

Visit 2 will entail the following procedures:

- Acquisition of the data download from the closed-loop system
- Acquisition of the data download from the SNAQ app (control group only)
- Feedback questionnaire on the SNAQ app (control group only)

At the end of the visit and throughout period 3, participants of the control group will undergo a period of 3 weeks without using the SNAQ app. The license for using the SNAQ app will be temporarily de-activated remotely.

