### **Visit 3 (control group only)**

Visit 3 will entail the following procedures:

- Acquisition of the data downloads (data from the closed-loop system and the SNAQ app)

After the last visit (Visit 2 for participants of the intervention group and Visit 3 for the control group) participants will continue to have free access to the premium version of the SNAQ app. Participants will not receive instructions on how to use the app during this period. Data on SNAQ app use during this period will be collected at the end of the period. At the end of this period, the study will be terminated and the study phones (if applicable) will be collected.

During the whole study duration, all participants will continue to use their usual diabetes therapy (including hybrid-closed loop system and the type of insulin). The study will not specify nor change any aspects related to the participants' insulin treatment settings. Whenever possible, the participant should not change their diabetes therapy during the course of the study due to the potential of confounding effects.

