| SNAQ instruction                                          |           | G1                  | G2                                          |                                             |                                             |                        |
| Meal management questionnaire                             |           | G1, G2              |                                             |                                             |                                             |                        |
| Nutrition literacy questionnaire                          |           | G1, G2              | G1, G2                                      |                                             |                                             |                        |
| Feedback questionnaire                                    |           |                     | G1                                          | G2                                          |                                             |                        |
| Data download (SNAQ, hybrid closed-loop pump)             |           | G1, G2              | G1, G2                                      | G1, G2                                      | G1, G2                                      | G2
(SNAQ data only) |
| Return of smartphone (if applicable)                      |           |                     |                                             |                                             | +                                           | +                      |
| Safety assessment                                         |           |                     | +                                           | +                                           | +                                           | +                      |

G1: Intervention Group (SNAQ in Period 1); G2: Control Group

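### The windows for sustainability endpoints 7-12 are anchored one visit too late and fall in the free-use period, not in the three weeks without the app

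*Protocol*

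**What the plan says.** The note under endpoints 7-12 (Protocol section 2.1, Secondary endpoints) says that glucose control at baseline and during app use will be "compared with the variables calculated during the 3 weeks following discontinuation of the app". It then fixes the days. One window runs from "Visit 2 + 1 Day to Visit 2 + 21 Days for the intervention group". The other is given in the same form, namely "Visit 3 + 1 Day to Visit 3 + 21 Days for the control group".

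The conduct sections place the stopping points elsewhere:

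- Section 3.3, Visit 1 (end of period 1): "At the end of the visit and throughout Period 2, participants in the intervention group will stop using SNAQ app". The licence is de-activated remotely.
- Section 3.3, Visit 2 (end of period 2): throughout period 3, "participants of the control group will undergo a period of 3 weeks without using the SNAQ app".
- Section 3.3, Visit 3: after the last visit, which is Visit 2 for the intervention group and Visit 3 for the control group, "participants will continue to have free access to the premium version of the SNAQ app".
- Section 2.2 attaches "weeks 4-6 for the intervention group and weeks 7-9 for the control group" to the sentence on the three-week discontinuation, and then offers both groups three further weeks of app use by preference.
- Appendix 1 labels the baseline visit V0 and limits the control group's end-of-study download to "SNAQ data only".

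**The concern.** In each group, the visit used as the anchor is the one that ends the off-app period, not the one that starts it. A script that follows the note would take the 21 days in which the app is on offer again and label them as the period after discontinuation.

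Two different harms follow, depending on the group:

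- **Where glucose data exist for the wrong window**, the values would look plausible. Any effect of renewed app use would be read as an effect that persisted after stopping. Because the note also compares this window with the app-use period, similar values in the two could be misread as full retention of benefit.
- **Where no glucose data are scheduled**, the endpoints could not be computed at all.

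Endpoints 7-12 are the only endpoints that serve the sustainability objective, so that objective depends entirely on this definition.

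**Working it through.** **Inputs**

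- Each period lasts 3 weeks (section 2.2).
- Baseline is V0 (Appendix 1). Visits 1 and 2 are the ends of periods 1 and 2 (section 3.3 headings). Visit 3 closes the control group's period 3.
- Taking baseline as day 0 and visits on schedule: Visit 1 = 21, Visit 2 = 21 + 21 = 42, Visit 3 = 42 + 21 = 63.

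**The timeline against the protocol's own total.** The control group has 3 weeks of usual practice, 3 with the app, 3 without and 3 of optional use: 3 + 3 + 3 + 3 = 12 weeks, the duration shown in Appendix 1. The intervention group has no initial waiting period, so its total is 3 + 3 + 3 = 9 weeks.

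**Stated windows against off-app periods** (window = anchor visit + 1 to anchor visit + 21)

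| Group | Window in the note | Days (weeks) | App stopped at | Off-app days (weeks) | Overlap |
|---|---|---|---|---|---|
| Intervention | Visit 2 + 1 to + 21 | 43-63 (7-9) | Visit 1 | 22-42 (4-6) | 0 of 21 |
| Control | Visit 3 + 1 to + 21 | 64-84 (10-12) | Visit 2 | 43-63 (7-9) | 0 of 21 |

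Both windows are late by exactly one period: 43 - 22 = 21 days and 64 - 43 = 21 days.

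**Can another reading rescue the labels?**

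- *Visit numbering.* The anchors would be right if baseline were Visit 1, but Appendix 1 calls it V0 and section 3.3 makes Visit 1 the end of period 1.
- *The weeks in section 2.2.* By grammar, the parenthesis could be attached to the app-use periods. The same section, however, puts app use in the first 3 weeks (intervention) and in weeks 4-6 (control). Under that reading the control group would also use the app in weeks 7-9, stop in weeks 10-12 and have its optional period in weeks 13-15, beyond the 12 weeks in Appendix 1.

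**Data scheduled for the stated windows**

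- *Control, days 64-84.* The end-of-study download excludes closed-loop data, and section 3.3 plans only app-use data for this period. Scheduled glucose data are nil. Section 4.2 discards a period with less than 30% of its data (0.30 × 21 = 6.3 days) and rules out imputation. The control group, 22 of the 44 planned participants, would therefore drop out of the pooled comparison in section 4.1.
- *Intervention, days 43-63.* Appendix 1 lists a closed-loop download for this group in the Visit 3 column, but section 3.3 restricts Visit 3 to the control group. If Appendix 1 is followed, values for the wrong window would exist.

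**Scope.** The secondary endpoints are numbered 2-12, which makes 11. Endpoints 7-12 are 6 of them.

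**After re-anchoring.** Visit 1 + 1 to + 21 gives days 22-42 (weeks 4-6). Visit 2 + 1 to + 21 gives days 43-63 (weeks 7-9). Both match the off-app weeks exactly.

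**The case against.** The strongest reply is that this is a slip in labels and not a choice of design. The note itself names the three weeks after discontinuation as its target, and section 4.1 repeats it, so a careful analyst might well pick the right days. That is a fair description of the error's origin. It does not remove the error: section 4.1 gives no dates, and section 3.3 says outcomes are calculated by custom scripts, which need dates. The note is the only place that supplies them.

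Three further points stand in part:

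- **The two harms do not coincide in one group.** With no glucose data after Visit 3, literal coding would return empty values for the control group, and the mistake would probably be noticed. Silent misreporting is mainly a risk in the intervention group, and only if the Visit 3 download in Appendix 1 is taken.
- **App use in the follow-up is optional**, so the degree of contamination is unknown. If nobody used the app, the window would cover days 22-42 after stopping instead of days 1-21. If everybody used it, the window would be wholly on-app. Neither is the stated estimand.
- **The parenthesis in section 2.2 is ambiguous** and may be where the wrong labels came from. It should be reworded as well.

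It is also true that the primary endpoint, its day 1-21 window, the randomisation and the sample size are untouched, and that the slip can be put right at any time before analysis.

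**Conclusion.** The concern holds. As written, the windows for endpoints 7-12 miss the off-app period completely (0 of 21 days in each group) and coincide with the optional-use follow-up. Six of the 11 secondary endpoints, all those for sustainability, are affected. For the control group, the stated window has no scheduled glucose data.

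The exact days assume visits held on schedule. The shift of one full period does not depend on this, because it follows from which visit starts and which visit ends the off-app period. The size and direction of any bias cannot be given, since they depend on how many participants take the app up again. The statistical analysis plan was not available, so whether it repeats the wrong anchors is unknown. The correction should be made before any sustainability endpoint is calculated.

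**What to change.** In the note to endpoints 7-12, define the post-discontinuation window as Visit 1 + 1 day to Visit 1 + 21 days for the intervention group, and Visit 2 + 1 day to Visit 2 + 21 days for the control group. Adding the study weeks (4-6 and 7-9) would guard against a repeat of the slip.

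Alongside this:

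1. Reword the sentence in section 2.2 so that the weeks in parentheses clearly belong to the period without the app.
2. Reconcile section 3.3 and Appendix 1 on whether the intervention group has a Visit 3 download, and state what that download is for.
3. Check that the statistical analysis plan and the analysis scripts use the corrected windows.

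The cost is a few sentences of text. The closed-loop data for the corrected windows are already due at Visit 2 (intervention) and Visit 3 (control), so no extra collection or participant burden is involved.
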